### Intervention

#### Operative technique

Patients in the intervention group are treated by AORIF, patients in the control group by ORIF. The operative treatment is performed by one of the foot and ankle surgeons. Slight differences in the operative procedure depend on fracture type and localisation. The standard operative protocol is the same in all patients no matter whether they are included in the study or not. It will be described in detail in the following.

#### Positioning

The positioning on the operating table depends on whether the posterior malleolus is addressed or not. If the posterior malleolus is not affected the patient is placed in supine position. If the posterior malleolus is addressed the patient is placed on the contralateral side in a so-called unstable lateral position. “Unstable” means that the patient is placed on the contralateral side, but 1) the leg is mobile so that ankle arthroscopy can easily be performed and 2) the patient can simply be turned into supine position after fixation of the posterior and lateral malleolus without changing the sterile cover.

#### Ankle arthroscopy

The arthroscopy is performed first. At this time the fractures are not fixed. Therefore, the joint is unstable and the entire tibiotalar joint can be evaluated without additional distraction. To avoid lesions of the cartilage and soft tissue, the joint is first inflated with saline, and the portals are created by blunt dissection. A 2.7 mm, 30° arthroscope is inserted into the ankle through a standard anteromedial portal. Afterwards the standard anterolateral portal is performed in the same way. A standardized systematic examination as described by Ferkel and Fasulo is regularly used to inspect the internal structures [18]. At this stage all loose bodies and disrupted ligaments extending into the joint are removed. If there are loose fragments that are big enough to be reduced and fixed, resorbable ethipins (Ethicon, Somerville, New Jersey, USA) are used. Chondral damage, if present, is treated according to the grade of damage. In the AORIF group a final examination is performed by ankle arthroscopy after fracture fixation. In this case, we use an elevatorium in order to assess the posterior aspects. Thereby the fracture reduction can be evaluated and all remaining loose bodies can be removed.

#### Classification and treatment of cartilage lesions

Lesions of the articular cartilage are graded according to depth (superficial, partial-thickness, full-thickness cartilage defect) and localization as determined by inspection and probing. The classification system postulated by ICRS (International Cartilage Repair Society) focussing on the lesion depth (grade 0–4) is applied [19]. Therapy depends on the grade of the cartilage lesion. Debridement of unstable edges is suggested for ICRS 2 lesions, whereas ICRS 3 and 4 lesions need further treatment. In these cases, chondroplasty and micro fracturing is applied.

### Fracture fixation

#### Posterior malleolus

Until now, there are no clear guidelines for the treatment of posterior malleolus fractures. Historically, the size of the fragment was the major determining factor [20, 21]. When evaluating the available literature, there is no hard evidence for these recommendations as they are only based on a small case series of eight patients by Nelson and Jensen in 1940 [22]. There is growing evidence, that there are more factors that have to be considered when determining appropriate management of posterior malleolus fractures – such as articular impaction, comminution, ankle congruity and syndesmotic stability. Ogilvie-Harris et al. could demonstrate that the posterior inferior tibio fibular ligament (PITFL) provides the major part of syndesmotic stability. This contribution to syndesmotic stability is disrupted when the posterior malleolus is fractured [23]. Principally, the syndesmotic stability can be restored by tibio fibular fixation or ORIF in case of a posterior malleolus fracture. Regarding transsyndesmotic screw fixation, Gardner et al. reported a syndesmotic malreduction rate after screw fixation of 52 % on postoperative CT evaluation [24]. They concluded that anatomic reduction and fixation of a posterior malleolus fracture is superior in re-establishing syndesmotic stability by restoring the length of the intact PITFL. Furthermore, anatomic reduction of the posterior malleolus fragment restores the relationship between the tibia and fibula and facilitates bone-to-bone healing [25]. Based on these considerations, we routinely perform open reduction and internal fixation of posterior malleolus fracture if the size of the fragment allows for it. We fix the posterior malleolus before addressing the fibula to allow adequate visualization of the reduction during x-ray imaging as the fibular plate often interferes with the fracture line on the lateral view [26]. We perform a posterolateral approach [27]. A longitudinal skin incision posterior to the peroneal tendons is performed. Retraction of the peroneal muscles and tendons ventrally visualizes the posterolateral edge of the distal tibia. Care is taken to preserve the PITFL attachment to the fragment and the joint capsule. In the next step, open reduction is performed using K-Wires to fix the anatomic reduction temporary. If the reduction is sufficient a titanium one-third tubular plate with two to four screws is used in an antiglide-technique to perform internal fixation (Fig. 1). If the fracture is simple with two fragments only and the fragment size is big enough two single lag screws are used.

**Fig. 1 Fig1:**
[figure not shown]
Intraoperative x-ray; **a** Lateral view with temporary k-wire fixation of the posterior fragment; **b** Lateral view after fixation with a three-hole one-third tubular plate for fixation of a posterior malleolus fracture

#### Lateral malleolus

If the patients suffer both, a fracture of the posterior and the lateral malleolus, both fractures can be stabilized using the same posterolateral approach. After fixation of the posterior malleolus as described above the preparation of the fibula fracture is performed. Therefore, we prepare a full-thickness-flap in the direction of the fibular superficial to the peroneal tendons (Fig. 2). According to fracture type and localization, we normally use a lag screw performed as it is described in the AO manual followed by a one-third tubular plate as a neutralization plate (Synthes, Umkirch, Germany). In case of a multifragmentary fracture, distal fracture or in case of osteoporotic bone a lateral locking plate or a locking hook-plate is used (Arthrex, München, Germany) (Fig. 3). If the patient only presents with a lateral malleolus fracture, a standard lateral incision is performed.

**Fig. 2 Fig2:**
[figure not shown]
The intraoperative image shows the posterolateral incision and a locking plate used for the lateral malleolus fracture (Arthrex, München, Germany) and one-third tubular plate used for the posterior malleolus fracture (Synthes, Umkirch, Germany)

**Fig. 3 Fig3:**
[figure not shown]
Intraoperative X-ray; Mortise view after fixation of the posterior malleolus with a with an three-hole antiglide-plate and a locking plate for the fracture of the lateral malleolus

#### Medial malleolus

Routinely, an incision beginning 1–2 cm distally to the tip of the medial malleolus over the medial malleolus in the direction of the middle of the distal tibia is performed. In the next step, we start with the exposure of the anterior-medial part of the fracture site with a limited arthrotomy to assure an anatomic reduction at the joint surface. K-wires are inserted perpendicular to the fracture plane and replaced by two cannulated leg screws after the anatomical reduction was proofed (Fig. 4). Washers are used in case of osteoporotic bone. If the fracture is comminuted, the fragment is very distal or small or the bone is osteoporotic, either a locking hook plate or medial tension band wiring is used.

**Fig. 4 Fig4:**
[figure not shown]
Intraoperative x-ray; **a** Mortise view with an antiglide-plate for the posterior malleolus, locking plate for the fracture of the lateral malleolus and additional temporary k-wire fixation of the medial malleolus. **b** postoperative CT-scan (coronar view) with an antiglide-plate for the posterior malleolus, locking plate for the fracture of the lateral malleolus and lag screw fixation of the medial malleolus

#### Syndesmotic complex

After all fractures have been stabilized, the stability of the syndesmotic complex is tested. Therefore, the “external rotation test” as described by Frick et al. is used [28]. This test is commonly used for the testing of syndesmotic stability. In case of persisting instability, the reduction of the distal tibiofibular joint is performed using a reduction clamp. The reduction is checked by an intraoperative CT-scan (Iso-C-3D, Ziehm Imaging, Nürnberg, Germany). If the reduction is sufficient, we position a TightRope® (Arthrex, München, Germany) 30° from posterior to anterior parallel to the tibial plafond with the ankle in neutral position.

#### Postoperative treatment

The postoperative protocol is the same for all fracture types included. All patients are treated following the same postoperative protocol – independent of study participation and allocation to the two different groups. Postoperatively, the ankle is routinely immobilised in a cast for 1 week. Directed-active and active-assisted range of motion exercises is performed immediately. Partial weight bearing (20 kg) is allowed for 6 weeks postoperatively followed by progressive weight bearing to tolerance.

### Study follow-up

#### Schedule of events and assessments

A subjective evaluation (questionnaires), physical examination and radiographic analysis are performed preoperatively and again 6 weeks, 6 and 12 months postoperatively. The further follow-up visits include yearly examination, as the long-term follow-up is essential regarding the outcome parameter of this trial (Schedule of events see Table 2). Patients enrolled in our study do not need any additional outpatient visits or radiographic investigations. The data that we obtain from the medical records include the patient’s age and sex, date of injury, date of surgery, classification of the ankle fracture, grade and locations of intra-articular lesions such as chondral lesions, loose bodies, ligamentous damage and presence or absence of concurrent synovitis, course of wound healing, pre- and posttraumatic activity level, time to return to work and sports and quality of life. Pseudonymization is performed for all patients’ details.

**Table 2 Tab2:** Schedule of events

Assessment	Screening	Enrolment	Surgery	6 weeks	6 months	12 months	Yearly follow-up
Screening form	x						
Informed consent	x						
Randomisation		x					
Baseline characteristics form		x					
Ankle characteristics/ Physical examination		x		x	x	x	x
Surgical form			x				
Arthroscopic findings form			x				
Perioperative form			x				
Follow-up form				x	x	x	x
X-ray/CT	x		x	x	(x)	x	(x)
Pain Visual Analogue Scale		x		x	x	x	x
Short-form 12		x		x	x	x	x
American Orthopaedic Foot and Ankle Society Score				x	x	x	x
Japanese Society of Surgery of the Foot Score				x	x	x	x
Olerud and Molander Score				x	x	x	x
Karlsson Score				x	x	x	x
Tegner Activity Scale		x		x	x	x	x
Complications			x	x	x	x	x

#### Subjective outcome assessment

In order to blind subjective evaluation, questionnaires are answered before physical examination is performed. Patients will answer questions about their general satisfaction, pain level (VAS), activity level and any complaints. The Short Form 12 (SF-12) [29] and the Tegner Activity Scale (TAS) [30] are filled in pre- and postoperatively.

#### Physical examination

For the physical examination blinding of the patients is not feasible as the arthroscopy portals are visible. The physical examination consists of the inspection of the hind foot including hind foot axis, ankle swelling and wound healing. The important anatomical landmarks are examined for any painful structure. Clinical tests involve medial and lateral ligament stability and non-weight bearing, assisted dorsal and plantar range of motion measured with a goniometer. The physical examination further includes functional outcome scores. The AOFAS Score (American Orthopaedic Foot and Ankle Society) [31], JSSF Score (Japanese Society of Surgery of the Foot) [32], OMAS (Olerud and Molander Score) [33], Karlsson Score are used to evaluate postoperative functional outcome.

#### Primary outcome

The AOFAS score is the primary outcome parameter. It is one of the most widely used scoring systems to evaluate functional ability and physical examination incorporated in a numeric scale. It has been widely adopted and has become an accepted standard of assessing patients after foot and ankle surgery. A validated German language version is used.

#### Secondary outcome

The JSSF, OMAS, Karlsson Score, TAS and SF-12 are recorded postoperatively. Further secondary outcome parameter are radiographic analysis, arthroscopic findings of intra-articular lesions, time to return to work/sports and complications.

#### Radiographic analysis

The radiographic assessments comprise the routine x-rays (non-weight bearing, a.p. and lateral) and a CT scan preoperatively and postoperatively. Postoperative radiographs and x-rays performed 6 weeks after the operation are non-weight bearing films. Beginning with 1-year of follow-up, weight-bearing films will be obtained. Position of implants, potential secondary dislocation and fracture consolidation/healing are evaluated and documented via radiographic analysis. The displacement of the fracture site is controlled fluoroscopically intra- and postoperatively; displacement is graded into three groups (no dislocation, dislocation ≤2 mm and dislocation >2 mm). In case sub-optimal reduction or malreduction ≥2 mm is recognized using intraoperative x-ray or arthroscopy, fixation will be removed and the reduction will be performed again. Thereafter the reduction is re-evaluated using x-ray and arthroscopy. If malreduction of ≥2 mm should be recognized in postoperative CT-scans revision surgery would be discussed with the patient. Radiographic assessment of posttraumatic osteoarthritis is performed according to the classification system by Kellgren et al. [34].

#### Fracture classification

Detailed description and classification of the fracture are performed using the AO classification system.

#### Arthroscopic findings

The appearance, description and classification of intra-articular findings in the arthroscopic group are documented. Detailed description of the lesion, capsular, ligaments, ventral syndesmosis, grading and localization of chondral lesions (ICRS classification), loose bodies is recorded and analysed. These intraoperative findings are further analysed according to fracture classification. In order to determine the frequency and distribution of the chondral lesions in the series, fractures of the same type will be grouped together and statistical analysis will be performed to compare these groups. In Fig. 5 two examples of intra-articular pathologies are presented.

**Fig. 5 Fig5:**
[figure not shown]
Exemplary arthroscopy images showing an osteochondral lesions grade 4 (ICRS) on the medial talus and loose bodies

#### Data and safety monitoring board

According to the Data and Safety Monitoring Board Guidelines (National Institute of Health, NIH) we establish a group of experts (experienced trauma surgeons, who are not involved in our study) who independently review and evaluate the accumulated study data for participant safety, study conduct and progress and also efficiency of our study. In detail, arthroscopical findings and arthroscopy-associated complications will be evaluated thoroughly after 15 patients in the intervention group (AORIF). Based on these results, they will make recommendations concerning continuation, modification or termination of the trial.

### Statistical analysis

Primary outcome of our study is the difference of the AOFAS score between the intervention (AORIF) and comparison (ORIF) group after a follow-up of 2 years. We expect a mean difference of four points between the AORIF and ORIF group showing better results in the AORIF group. This expectation is feasible on the basis of the existing data (see [3] and [1]). The statistical calculation was performed with an expected correlation of 0.5 between the two groups. Based on a conservative estimation of the observed standard deviation of the AOFAS score in a comparable population (see [3] and [1]), we expect a standard deviation of six for the AOFAS score in our population. Based on the supposed correlation of 0.5 the standard deviation of the differences regarding our primary outcome is also expected to be not more than six. Therefore, each group has to contain 37 patients in order to find a difference of four between the two groups with a level of significance of 5 % and a power of 80 % and a standard deviation of six. In case of subgroup analysis, Shapiro-Wilk and Levene tests will be used to test normality and equality of variances. Subgroup analysis will be conducted using Student’s t-test, Pearson Chi-Square or ANOVA where appropriate. Statistics will be calculated using SPSS 22.0 (SPSS Inc. Chicago, Illinois 60606).

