**Methods/design:**

We perform a randomised controlled trial at Munich University Clinic enrolling patients (18–65 years) with an acute ankle fracture (AO 44 A2, A3, B2, B3, C1 - C3 according to AO classification system). Patients meeting the inclusion criteria are randomised to either intervention group (AORIF, *n* = 37) or comparison group (ORIF, *n* = 37). Exclusion criteria are fractures classified as AO type 44 A1 or B1, pilon or plafond-variant injury or open fractures. Primary outcome is the AOFAS Score (American Orthopaedic Foot and Ankle Society). Secondary outcome parameter are JSSF Score (Japanese Society of Surgery of the Foot), Olerud and Molander Score, Karlsson Score, Tegner Activity Scale, SF-12, radiographic analysis, arthroscopic findings of intra-articular lesions, functional assessments, time to return to work/sports and complications. This study protocol is accordant to the SPIRIT 2013 recommendation. Statistical analysis will be performed using SPSS 22.0 (IBM).

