### Patient selection

#### Eligibility criteria

Patients aged 18–65 years with an acute ankle fracture (AO 44 A2, A3, B2, B3, C1-C3) according to the judgment of the surgeons of the foot and ankle team of our level I trauma centre are enrolled in the trial. Fractures are evaluated and graded according to classification reported by AO Foundation. Patients are informed about our current investigation by detailed patient information. Only patients, who confirm in study participation and in the operative procedure, are enrolled. To avoid misclassification, all radiographs are evaluated by at least two orthopaedic surgeons. Disagreements are resolved by discussion. Only patients with a maximum interval of 2 weeks between injury and intervention are included. All patients included must be able to understand the meaning of the trial and its consequences. Written informed consent is mandatory. No additional investigation (clinical or radiographic investigation) will take place if the patient is included compared to patients who refuse inclusion. A list of inclusion and exclusion criteria can be found below (Table 1). Open fractures are excluded. Also, patients with a high risk of anaesthesiology problems (i.e., ASA risk score >3), acute infection, mental illness or low expected compliance are excluded from trial participation. If patients issue a certain treatment preference, they are excluded as well. Patients are further asked for diabetes and smoking as these are possible confounders for the outcome. Moreover, previous ankle injuries are documented in all patients.

**Table 1 Tab1:** Inclusion and Exclusion criteria

Inclusion criteria	Exclusion criteria
Age 18–65 years	Patients under 18 years or over 65 years
	Patients who have acute infections, mental illnesses, high anesthesiological risk (ASA >3)
	Patients with expected incompliance
Acute ankle fracture classified as AO type 44 A2, A3, B2, B3, C1-C3	Acute ankle fracture classified as AO type 44 A1 or B1 fracture, pilon or plafond-variant injury. Open fractures
Written informed consent (patient is able to read and understand German language properly)	Patients without written informed consent

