#### Patient recruitment and screening

All patients presenting to participating surgeons with an acute ankle fracture are screened for participation in the trial. Such patients are classified as 1) excluded, if they do not meet the eligibility criteria; 2) missed, if they are presumed eligible but missed due to error or staff availability; or 3) included (eligible and randomised). Study personnel obtain written informed consent from all eligible patients.

In all patients, fractures are initially reduced, followed by plaster cast stabilization or - if this does not sufficiently reduce the fracture - by external fixator. The surgeon on charge with proven expertise in reduction and casting maneuvers performs the reduction and casting. Patients are admitted to the trauma ward afterwards in order to elevate the leg to reduce the swelling around the ankle. Operation will be performed when swelling is reduced to an acceptable level. The patient’s skin is assessed preoperatively ensuring adequate skin wrinkling.

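### The 37 patients per group needed for 80% power are also the number randomised, so the stated power at 2 years holds only with virtually complete follow-up

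*Protocol article*

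**What the plan says.** The Statistical analysis section of the protocol article defines the primary outcome as the difference in AOFAS score between the arthroscopically assisted group (AORIF) and the open group (ORIF) at 2 years. The planning values are given there:

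- the difference: "We expect a mean difference of four points between the AORIF and ORIF group";
- the test level: "with a level of significance of 5" per cent;
- the remaining inputs: "a power of 80 % and a standard deviation of six".

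The resulting requirement is that "each group has to contain 37 patients in order to find a difference of four between the two groups".

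The Methods/design part of the abstract says that eligible patients are "randomised to either intervention group (AORIF, *n* = 37) or comparison group (ORIF, *n* = 37". The number required for the analysis and the number entering the trial are therefore the same. The article states no expected attrition, no inflation of the sample size and no replacement of lost patients.

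The AOFAS score is listed under Physical examination, so it is obtained at a visit. Table 2 schedules it at 6 weeks, 6 months, 12 months and yearly after that; the 2-year value comes from the first of the later yearly visits.

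**The concern.** A sample-size formula gives the number of patients with an outcome, not the number to be randomised. The two can coincide only if nobody is lost, or if the formula's answer already has room in it. Here the endpoint needs attendance 2 years after trauma surgery in patients aged 18 to 65, and some loss is to be expected. If 37 is the bare requirement, the 80% describes a trial with almost complete follow-up, and the trial as actually run will have less. The consequence is a higher chance of missing a true 4-point benefit than readers are told. The size of a valid test would not be affected.

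**Working it through.** **Inputs.** Difference 4, SD 6, significance 5%, power 80% (all from Statistical analysis); 37 randomised per group (abstract). Sidedness is not stated. I take it as two-sided, because a one-sided test would need only about 28 per group and would not give 37.

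**Reproducing the plan's figure.**

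Normal approximation: n = 2 × SD² × (1.960 + 0.842)² / difference² = 2 × 36 × 7.85 / 16 = 35.3, rounded up to 36.

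Exact two-sample t-test: the noncentrality is 4 / (6 × √(1/n₁ + 1/n₂)) with n₁ + n₂ − 2 degrees of freedom. At 37 per group this is 4 / (6 × √(2/37)) = 2.867, giving power 80.8%. At 36 per group it is 2.828, giving 79.7%. The smallest size that reaches 80% is therefore 37, which is the plan's number. No loss factor is needed to get there, so none is hidden in it.

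The section also mentions a correlation of 0.5 between the groups. Correlation has no role for two independent groups, and 37 is obtained without it. A paired calculation with SD of differences 6 would need only 20 pairs, so that is not where 37 comes from.

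**Effect of the first losses** (same formula):

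| Evaluable | Power |
|---|---|
| 37 and 37 | 80.8% |
| 37 and 36 | 80.2% |
| 36 and 36 | 79.7% |
| 37 and 35 | 79.6% |

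**Effect of assumed 2-year losses.** The rates are my assumptions. Evaluable numbers are 37 × (1 − loss), rounded down.

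| Assumed loss | Evaluable per group | Power | Randomised per group to keep 37 evaluable |
|---|---|---|---|
| 5% | 35 | 78.5% | 37/0.95 → 39 |
| 10% | 33 | 76.0% | 37/0.90 → 42 |
| 15% | 31 | 73.3% | 37/0.85 → 44 |
| 20% | 29 | 70.4% | 37/0.80 → 47 |

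**What a repeated-measures model can recover.** Suppose 20% are lost, all after the 12-month visit, and the 12-to-24-month correlation r is between 0.5 and 0.8 (assumptions). The variance of the 24-month group mean is then SD² × [(1 − r²)/29.6 + r²/37], where 29.6 = 37 × 0.80.

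- r = 0.5: effective n = 1 / (0.75/29.6 + 0.25/37) = 31.2 per group, power about 73.5%.
- r = 0.8: effective n = 1 / (0.36/29.6 + 0.64/37) = 33.9 per group, power about 77%.

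Without rounding down, complete cases (29.6 per group) give about 71%. The gain is real but stops short of 80%, and it is smaller if patients leave earlier.

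**The case against.** **No figure is miscalculated.** That is correct: 37 is the right answer to the calculation as posed. The defect is that it is also used as the number to randomise.

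**An article condenses the full protocol, so an allowance might sit there.** That would be a fair defence if the article gave only the required number. It also prints the number randomised, and that number is the same 37.

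**The shortfall rests on assumed loss rates and may be small.** This stands in part. At 5% loss the power is only 1.5 points below 80%. The article calls its SD conservative; if the true SD were 5.5 (an assumption), 31 evaluable per group would still give 80.4%. It also excludes patients with low expected compliance and asks for no extra visits, both of which favour retention. None of this makes the stated power correct at the stated SD once a second patient is lost.

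**Two stronger readings are tempting and should not be made.** One is that any loss at all takes the trial below 80%. It does not: with a single patient missing, power is still 80.2%.

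The other is that the plan produces its own exclusions after randomisation. Table 2 places randomisation at enrolment, in a column before surgery; Eligibility criteria says "Only patients with a maximum interval of 2 weeks between injury and intervention are included"; and Patient recruitment and screening says "Operation will be performed when swelling is reduced to an acceptable level". A reader might infer that patients with persistent swelling are randomised and then removed, compromising the randomised comparison. The article does not say so. The interval is an inclusion criterion, included patients are defined as those both eligible and randomised, Table 2 gives no time between enrolment and surgery, and nothing withdraws a randomised patient. The text only leaves open when, between enrolment and surgery, the envelope is opened.

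**Conclusion.** The concern holds as a statement about power. The 37 per group is the uninflated requirement and also the number randomised, so the 80% at 2 years is true only with virtually complete follow-up: at most one patient missing out of 74 by the exact t-test. By the normal approximation the margin is slightly wider (80.7% at 36 per group, 79.6% at 35), which does not alter the conclusion. For assumed losses of 5% to 20%, power lies between about 78.5% and 70.4%. These values assume a true difference of 4, an SD of 6, a two-sided 5% test, equal loss in both groups and an analysis of observed 2-year scores only. This is a power statement to be corrected; it is not evidence of bias in the randomised comparison.

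**What to change.** 1. State that 37 per group is the number evaluable at 2 years, and restate the power at the loss the sponsor expects, with the basis for that rate. On the assumptions above this would read, for example, about 76% at 10% loss or about 70% at 20%. The cost is a text change and a less favourable power statement.

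2. In addition, the AOFAS scores at 6 weeks, 6, 12 and 24 months can be analysed in a repeated-measures model of all randomised patients, with the 24-month contrast as the estimate. This uses data already scheduled and lets patients lost late contribute. It should be presented as recovering part of the loss, not as restoring 80%. If the analysis plan, which is not shown, already specifies such a model, only the power statement needs to change.

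If the sponsor wishes to keep 80% itself, the number randomised would have to rise, for example to 42 per group (84 in total) at 10% loss or 47 per group (94 in total) at 20%. That costs recruitment and time, and is the sponsor's choice.
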